## Abstract

**Introduction:**

Primary biliary cirrhosis (PBC) is an autoimmune liver disease with approximately 50% of patients experiencing fatigue. This can be a particularly debilitating symptom, affecting quality of life and resulting in social isolation. Fatigue is highlighted by patients as a priority for research and patient support groups were involved in designing this trial. This is the first randomised controlled trial to investigate a treatment for fatigue in PBC. The trial protocol is innovative as it utilises novel magnetic resonance spectroscopy (MRS) techniques as an outcome measure. The protocol will be valuable to research groups planning clinical trials targeting fatigue in PBC and also transferrable to other conditions associated with fatigue.

**Methods and analysis:**

RITPBC is a Medical Research Council (MRC) and National Institute for Health Research (NIHR) Efficacy and Mechanism Evaluation Programme (EME)-funded project. It is a phase II, single-centre, randomised controlled, double-blinded trial comparing rituximab with placebo in fatigued PBC patients. 78 patients with PBC and moderate to severe fatigue will be randomised to receive two infusions of rituximab or placebo. The study aims to assess whether rituximab improves fatigue in patients with PBC, the safety, and tolerability of rituximab in PBC and the sustainability of any beneficial actions. The primary outcome will be an improvement in fatigue domain score of the PBC-40, a disease-specific quality of life measure, evaluated at 12-week assessment. Secondary outcome measures include novel MRS techniques assessing muscle bioenergetic function, physical activity, anaerobic threshold and symptom, and quality of life measures. The trial started recruiting in October 2012 and recruitment is ongoing.

**Ethics and dissemination:**

The trial has ethical approval from the NRES Committee North East, has Clinical Trial Authorisation from MHRA and local R&D approval. Trial results will be communicated to participants, presented at national and international meetings and published in peer-reviewed journals.

**Trial registration number:**

ISRCTN03978701.

Strengths and limitations of this studyRITPBC is the first randomised controlled trial of a treatment for fatigue in patients with primary biliary cirrhosis (PBC).The trial describes novel mechanistic outcome measures using magnetic resonance spectroscopy (MRS).Novel recruitment strategies utilising the UK-PBC trials platform are described.The main limitation is the responsivity of the primary outcome measure to meaningful improvement in fatigue. Responsivity is one of the 6 psychometric properties of any measure and determines its ability to measure meaningful change in a symptom in response to effective therapy. It is the untested one for the PBC-40 fatigue domain for the obvious reason that there is no therapy able to improve fatigue to allow us to test it. We have mitigated against this by having an objective measure as well (activity) and biomarkers (MRS).

## Background

Primary biliary cirrhosis (PBC) is a chronic cholestatic liver disease with a prevalence of 30/100 000.^1^ It affects approximately 20 000 people in the UK, predominantly females (10:1).^2^ PBC has an autoimmune aetiology with the majority of patients expressing autoantibodies directed against mitochondrial and nuclear antigens,^3^ and has strong associations with other autoimmune diseases^4^ PBC is characterised by inflammation and subsequent loss of the small intrahepatic bile ducts. Despite its name only a small number of patients will progress to cirrhosis and end-stage liver disease and a number of these will require liver transplantation.^5^ There is only one licensed treatment, ursodeoxycholic acid (UDCA), which slows progression of liver disease.^6^

PBC is associated with a number of symptoms including fatigue, cognitive impairment and pruritus. There are treatments available for PBC-associated pruritus but at present there are no licensed treatments for fatigue or cognitive dysfunction. Fatigue, which patients describe as physical exhaustion or their ‘batteries running down’, can be a very debilitating symptom. Fatigued patients are often unable to carry out normal day-to-day activities and frequently are unable to work resulting in a negative impact on quality of life.^7^ Recent data suggests that when patients have social isolation in combination with fatigue, there is a negative impact on quality of life.^8^ One patient with PBC has very eloquently described the impact of fatigue from PBC and the loneliness, frustration and despair that can result.^9^ In addition to the impact on the patients and their friends and family, fatigue is associated with economic costs (loss of earning, paying for assistance). Interestingly, fatigue is not related to the severity of liver disease^10^ and is unresponsive to UDCA therapy,^11^ suggesting that the processes responsible for fatigue in PBC are linked to the condition but not directly to liver injury.

There have been many advances in our understanding of fatigue over the years, starting initially with recognising it as a symptom associated with PBC, and then appreciating the scale of the problem^10^ and the impact it has on the patient's quality of life.^8^ Fatigue is a subjective symptom and not particular easy to study in clinical trials, and therefore the development and validation of the PBC-40, a disease-specific quality of life questionnaire, provides a key tool for studying fatigue in PBC.^12^ Studies have improved our understanding of the potential mechanisms driving fatigue in PBC and culminated in this clinical trial of rituximab. MRI studies point to an abnormality in muscle bioenergetic function as a potential cause of fatigue in PBC. Using the methods of phosphorous magnetic resonance spectroscopy (31P-MRS) they have demonstrated excessive intramuscular acidosis during and in the recovery from exercise. The severity of fatigue that patients describe is associated with the length of time that the acidosis is present and the recovery time back to the baseline pH.^13^ As a result of these observations, we hypothesise that the antimitochondrial antibodies which are seen in over 90% of people with PBC lead to over-utilisation of anaerobic pathways through their activity against pyruvate dehydrogenase (PDH). This is supported by MRS studies which have shown that mitochondrial dysfunction is directly related to antimitochondrial antibody (AMA) levels.^14^ Unpublished data from the Newcastle group have demonstrated significantly lower anaerobic threshold (AT) values compared with patients with age-matched and sex-matched primary sclerosing cholangitis (PSC) and sedentary controls, again supporting a muscle bioenergetic abnormality contributing to the fatigue seen in PBC. These findings support a trial to investigate rituximab, an anti-CD20, B-cell depleting monoclonal antibody as a potential treatment for fatigue in PBC.

To date there have been two pilot studies of rituximab in PBC.^15^
^16^ Neither had fatigue as a primary outcome measure, and instead focused on UDCA-unresponsive disease and biochemical outcomes. Both studies found that rituximab resulted in an improvement in liver biochemistry and is safe and well tolerated in PBC. The pilot study in Canada reported a clinically significant reduction in fatigue but the trial was not optimised for the study of fatigue and did not include fatigue in the inclusion criteria, therefore potentially underestimating the clinical effect of rituximab on fatigue.^16^

The RITPBC trial aims to investigate rituximab as a treatment for fatigue in PBC. RITPBC will provide important data on the efficacy, safety and tolerability of rituximab in PBC, as the pilot studies have suggested there may be a role for rituximab in treating UDCA-unresponsive disease. The second and important aspect of the trial will be the mechanistic data which aims to gain a better understanding of the mechanisms underpinning fatigue in PBC, and if a benefit is seen, to establish the mechanism of action. The novel MRS techniques used as a secondary outcome measure are unique to this trial. Given that fatigue is not specific to PBC, any advances in the understanding of the mechanisms of this symptom are likely to be transferrable to other conditions associated with fatigue.

Research has been moving forward over the past 20 years to improve our understanding of the impact of fatigue and identify potential mechanisms but clinical trials of therapeutic agents have been lacking. Patients highlight fatigue as a priority for research and close working with the patient support groups re-iterates that trials and subsequent treatments for fatigue are much needed. RITPBC is the first randomised controlled trial of a therapeutic agent to target fatigue in PBC. RITPBC also pilots novel recruitment techniques through utilisation of the UK-PBC stratified medicine trials platform. If this recruitment strategy proves successful it has the potential to revolutionise trials in PBC and provide an approach for trial recruitment transferrable to any rare disease. This article discusses the protocol design and methodology and will hopefully aid further trials to target fatigue in PBC as well as being transferrable to the many other conditions that have fatigue as a prominent symptom.

## Methods/design

### Study design

RITPBC is a phase II, single-centre, randomised controlled, double-blinded trial comparing rituximab with placebo in fatigued PBC patients. A total of 78 patients (39/arm) with definite or probable PBC and moderate–severe fatigue (PBC-40 fatigue domain score >33) will be recruited. The primary outcome is improvement in fatigue severity, assessed using the PBC-40, a disease-specific quality of life measure,^12^ which will be evaluated at baseline and at 12 weeks. The secondary objectives will be to explore the extent to which any such improvement in fatigue is related to a reduction in the level of anti-PDH antibody and to any associated effect on biomarkers of bioenergetic function assessed using novel MRS protocols. Other secondary outcome measures are improvement in AT, physical activity levels, liver biochemistry, daytime somnolence, autonomic symptoms, functional status, cognitive dysfunction and anxiety and depressive symptoms. The safety of rituximab in PBC will be explored and the sustainability of any beneficial actions evaluated.

### Screening, recruitment and consent

Recruitment will principally be from the large clinical cohort under follow-up at the Joint Autoimmune Liver Disease Clinic in the Newcastle upon Tyne Hospitals NHS Foundation Trust (>500, the largest clinical PBC service in the UK). Participant Identification Centres (PICs) in hospital trusts in the North of England will be opened to aid recruitment. Articles will be written for the patient support group LIVErNORTH and PBC Foundation and published in their newsletters and magazines. This trial is unique as it was the first trial to utilise the UK-PBC platform for recruitment to trials. UK-PBC is a £5 million Medical Research Council (MRC)-stratified medicine trials platform which holds genetic, symptom and biochemical data on over 3000 patients with PBC in the UK. Patients recruited to UK-PBC have consented to be contacted about trials and can therefore be easily accessed and recruited. The UK-PBC database can be searched for patients with a PBC-40 fatigue domain score >33. The clinicians looking after these patients can then be contacted and can approach the patients to see if they would be interested in taking part in the trial. This recruitment strategy targets patients with moderate to severe fatigue on a national level that would be impossible to do in a single-centre trial.

Potentially eligible participants are given a study Participant Information Sheet (PIS) after which they will have a minimum of 48 h to consider this information before written informed consent is obtained.

Participants will have a diagnosis of definite or probable PBC established using recognised epidemiological criteria.^17^
^18^

### Eligibility criteria

**Inclusion criteria**Age ≥18 yearsPatient has capacity and provided written informed consent for participation in the study prior to any study-specific proceduresModerate or severe fatigue as assessed using previously designated cut-offs of the PBC-40 fatigue domain score (ie, fatigue domain score >33)Presence of AMA at a titre of >1:40Adequate haematological function haemoglobin >9 g/L, neutrophil count >1.5×10^9^/L, platelet count >50×10^9^/LBilirubin <50 µmolInternational normalised ration ≤1.5Child-Pugh score <7Eastern Cooperative Oncology Group (ECOG) performance status <2Adequate renal function; Cockcroft and Gault estimation >40 mL/minWomen with child-bearing potential should have a negative pregnancy test prior to study entry and be using an adequate contraceptive method which must be continued for 12 months after completion of treatment**Exclusion criteria**History or presence of other concomitant liver diseases (including hepatitis due to hepatitis B or C or evidence of chronic viraemia on baseline screening), primary sclerosing cholangitis or biopsy-proven non-alcoholic steatohepatitisAverage alcohol ingestion >21 units/week (male) or >14 units/week (female)Chronic sepsis or intercurrent condition likely to predispose to chronic sepsis during the studyPrevious history of aberrant response or intolerance to immunological agentsPresence of significant untreated intercurrent medical condition itself associated with fatiguePresence of significant risk of depressive illness (Hospital and Anxiety and Depression Scale (HADS) score indicating caseness)Current statin therapy or statin therapy within 3 months of enrolmentOngoing participation in other clinical trials or exposure to any investigational agent 4 weeks prior to baseline or within <5 half-lives of the investigational drugMajor surgery within 4 weeks of study entryVaccination within 4 weeks of study entry; patients requiring seasonal flu or travel vaccines will be required to wait a minimum of 4 weeks postvaccination to enrol in the studyPregnant or lactating womenPsychiatric or other disorder likely to impact on informed consentThe patient is unable and/or unwilling to comply with treatment and study instructionsAny other medical condition that, in the opinion of the investigator, would interfere with safe completion of the studyHypersensitivity to the active substance (rituximab) or to any of the excipients (sodium citrate, polysorbate 80, sodium chloride, sodium hydroxide, hydrochloric acid, water (for injection)) or to murine proteinsActive, severe infections (eg, tuberculosis, sepsis or opportunistic infections)Known HIV infectionClinical history of latent tuberculosis infection unless the patient has completed adequate antibiotic prophylaxisAlanine transaminase (ALT)/aspartate transaminase (AST) 4× upper limit of normalSevere immunocompromised stateSevere heart failure (New York Heart Association (NYHA) Class IV) or severe uncontrolled cardiac diseaseMalignancy (other than basal cell carcinoma) within the last 10 yearsDemyelinating diseasePrevious participation in this studyAny contraindication to rituximab therapy not covered by other exclusions

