## Discussion

Over recent years, there have been many advances in gaining a better understanding of fatigue in PBC. We now appreciate what a significant problem it is, both in terms of the prevalence of fatigue as a symptom as well as the impact that it can have on the patient's lives. Although the pathophysiology of fatigue is not entirely understood research has enabled us to have a much better understanding of the potential causes of fatigue in PBC and possible targets for treatment. Given the recent increases in our understanding of fatigue the next step was to design and deliver a trial of a therapeutic agent aimed to improve fatigue in PBC which would also improve our understanding of the mechanisms of fatigue.

The trial is designed to provide useful information about the physiological effects of fatigue, the pathophysiology of fatigue as well as assessing the role of rituximab in treating fatigue.

Fatigue is a subjective symptom and is not always an easy symptom to study in a trial, which is why the protocol of this trial has been published with the hope of aiding others who may wish to design and deliver trials on fatigue in PBC as well as the many other conditions that have fatigue as a key symptom. The trial also incorporates novel techniques that can provide objective data on fatigue (MRS, AT and physical activity monitoring) as well as describing new recruitment techniques using national disease-specific databases. Forty patients have now received either rituximab or placebo infusions as part of the trial which make it the largest biological trial in PBC. We believe the high number of patients recruited to this trial is because we are addressing fatigue which is the issue that matters most to patients.

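### The haemoglobin inclusion limit is printed as more than 9 g/L (0.9 g/dL), which no candidate could fail; it is probably a unit slip for 9 g/dL (90 g/L)

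*Protocol article*

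**What the plan says.** The inclusion list under Eligibility criteria in the protocol article has one line on haematological function, containing three limits. The first is haemoglobin, printed as "haematological function haemoglobin >9 g/L, neutrophil count". The other two are a neutrophil count above 1.5×10^9/L and a platelet count above 50×10^9/L. The same list requires capacity and written consent, an ECOG performance status below 2, and a PBC-40 fatigue domain score above 33.

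Two exclusions in the same section bear on anaemia without naming it or giving a number. One covers significant untreated illness that itself causes fatigue. The other covers any further condition that "in the opinion of the investigator, would interfere with safe completion" of the study.

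No other section states a haemoglobin limit or uses another unit for it. The abstract presents the article as a model for later trials: "The protocol will be valuable to research groups planning clinical trials targeting fatigue in PBC".

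**The concern.** A criterion meant to secure adequate haematological function should be one that some candidates can fail. A haemoglobin limit of 9 g/L cannot be failed by anyone well enough to be screened. Either the number or the unit is wrong.

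This matters more here than it would in many trials. Anaemia can cause fatigue, and fatigue is both a condition of entry and the primary outcome. It could also bear on the anaerobic threshold and physical activity outcomes. A working haemoglobin floor helps to keep fatigue from another cause out of the sample. If the printed limit were applied literally, that safeguard would be missing and only the two unquantified exclusions would remain. A group taking the criterion over as printed would also take over a limit that does nothing.

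**Working it through.** **Inputs, all from Eligibility criteria unless stated**

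- Haemoglobin limit as printed: more than 9 g/L.
- Companion limits: neutrophils above 1.5×10^9/L, platelets above 50×10^9/L.
- Consent with capacity, and ECOG below 2.
- Conversion: 1 g/dL = 10 g/L.

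**Step 1: what the printed limit means.** 9 g/L ÷ 10 = 0.9 g/dL. A haemoglobin at or below this is not compatible with life. A person with capacity to consent and an ECOG status below 2 must lie above it, so the proportion of candidates it can exclude is nil. This step does not depend on what value was intended.

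**Step 2: the likely intention.** If the number 9 is right and the unit is wrong, the limit is 9 g/dL, and 9 × 10 = 90 g/L. The printed limit is then too low by a factor of 90 ÷ 9 = 10. The article does not confirm this, so it is an assumption.

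**Step 3: is it a fault of text extraction?** The rest of the line is intact. The neutrophil and platelet limits have workable values and units, so one of three limits is unworkable and two are sound. Nothing is broken or blacked out at that place. The next criterion, for bilirubin, gives micromoles without a volume. This suggests loose handling of units in this list and makes a slip confined to the article plausible, without proving it.

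**Step 4: do other criteria replace the limit?**

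| Criterion | What it covers | What it leaves open |
|---|---|---|
| Untreated condition associated with fatigue | Significant untreated anaemia; mandatory | Treated anaemia; no number |
| Investigator's opinion on safe completion | Any condition, treated or not, judged unsafe | Safety only, not confounding of fatigue; no number |
| ECOG below 2 | Works against severely symptomatic anaemia | Anaemia with better function; no number |

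Together they give partial cover.

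**Step 5: does it touch the statistics?** The sample size section uses an SD of 8, a baseline to follow-up correlation of 0.6, a difference of 5, 90% power and a 5% significance level. The ANCOVA residual SD is 8 × √(1 − 0.6²) = 6.4. Then n = 2 × (1.96 + 1.28)² × 6.4² ÷ 5² = 34.4, rounded up to 35 per arm. Allowing for 10% attrition, 35 ÷ 0.9 = 38.9, or 39 per arm and 78 in total. This reproduces the stated figures, and haemoglobin enters nowhere. The ANCOVA on baseline and 12-week scores is likewise unaffected.

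**Step 6: can an effect on enrolment be estimated?** No. The article reports no haemoglobin data.

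**The case against.** The strongest reply is that this is a misprint in a journal article and no flaw in the trial. The article has other slips of wording and the incomplete bilirubin unit, and it condenses a full protocol that is not shown. A limit of 0.9 g/dL is so implausible that any clinician would notice it and read it as 9 g/dL, so it is less likely to mislead than a plausible but wrong threshold. A group reusing the design would probably correct it too. The other exclusions would catch much of what a haemoglobin floor is for. Allocation is randomised and double-blind, which limits confounding of the comparison by anaemia. Nothing shows that a limit of 90 g/L would have changed anyone's eligibility.

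Most of this stands, and it keeps the point minor. The article does not show that the working documents carried the error, and no harm to the trial is demonstrated. The argument does not rescue the printed text, though. Saying that staff would read 9 g/dL concedes that the criterion is wrong as written. The article chose to state this number, so the full protocol cannot be said to have been left to supply it. The other exclusions supply no number and do not fully cover treated anaemia.

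**Conclusion.** The concern holds. As printed, the haemoglobin limit excludes nobody, and nothing else in the article corrects it. That conclusion rests only on the unit conversion and on the fact that no one at or below 0.9 g/dL could be a candidate, so confidence in it is high.

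The tenfold size of the error assumes that 9 g/dL was meant. Whether the slip goes beyond the article, and whether any participant was affected, cannot be settled from this document. With the power calculation and the primary analysis unchanged, and partial cover from other criteria, the severity is minor.

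**What to change.** Check the intended limit against the full protocol and the eligibility checklist used at screening, then correct the printed criterion. If 9 g/dL is confirmed, it should read haemoglobin >90 g/L (or >9 g/dL). Complete the bilirubin unit in the same correction; that is purely clerical.

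If the working documents already carry the right limit, the cost is a correction of one number or unit in the article, plus the bilirubin unit. Only if they also carry 9 g/L should they be amended and the screening haemoglobin of participants already randomised be reviewed. That look-up would be small: the Discussion states that "Forty patients have now received either rituximab or placebo infusions". Recruitment was still open at submission, so a corrected limit could still be applied to later entrants.
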